*Social relationships*. Relatively little is known about how quitting smoking affects social relationships (e.g., marital satisfaction, or satisfaction with, or structure of, a person’s social network113). For example, it is not known whether quitting smoking changes the nature of social networks or satisfaction with such networks. Does quitting, in fact, cause smokers to lose smoking friends, or does a smoker’s quitting cause friends to be more likely to quit themselves? An important and related question is whether cessation has long-lasting effects on marital/partner relationships. To the extent that quitting affects mental health status (or stress level) it may indirectly affect marital/partner relationships. Also, while it is clear that having a smoking spouse makes it more likely that a person will relapse, it is unclear whether one spouse successfully quitting increases the likelihood that his/her partner will quit. Finally, it is important to assess social relationship factors because they can play such a strong role in influencing risk and progression for other disorders. For instance, supportive relationships such as marriage are associated with longer life and less severe disease.114-116 Many of these questions can be best addressed through a prospective study of social networks.

*Stress.* Some information shows that although smokers report more stress than nonsmokers, their stress levels fall once they quit smoking.117,118 Chassin et al.119examined self-reports of stress among those who successfully quit smoking (n = 88) in a cohort study. In comparison to continuing smokers, quitters showed decreased stress from pre- to post-quit. Cessation may reduce stress because smoking is associated with social stigma, opponent-processes that may produce acute stress,9,120 worries about disease, and the prospect of having to quit.

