**Importance of the Proposed Research to Science and the Public Health**

This research may yield the best long-term information to date on both the physiologic benefits and costs of successful and unsuccessful attempts to quit smoking. It will make important contributions to descriptive psychopathology. It will provide the most fine-grained and accurate information to date on the histories of quitters and relapsers after a quit attempt.

This research will not only characterize the fates of smokers who are successful and unsuccessful in a quit attempt, but will also shed light on mechanisms that mediate observed outcomes. Observed mediational relations may suggest the importance of comprehensive interventions148-150 that can mitigate or prevent negative outcomes of cessation, or enhance positive outcomes. Application of such interventions would be greatly aided by identification of individuals most likely to experience important outcomes of cessation or continued smoking.

This research will also elucidate the precipitants of late relapse - - relapse occurring after the first year of abstinence. Additionally, this research will examine genetic correlates of outcomes such as ability to quit smoking and remain smoke-free, severity of nicotine dependence, severity and patterning of withdrawal symptoms, weight gain, psychiatric diagnoses/symptom profiles, and progression/status of smoking-related disease. Finally, this research may yield information that enhances smokers’ motivation to quit. Smokers may be more likely to make a quit attempt if they believe that smoking cessation will lead to greater life satisfaction, reduced sadness and worry, improved social relations and clinically significant reductions in risk of heart attack and stroke.

It is clear that the information to be gathered is of substantial public health importance. Since 50 million current tobacco users in America are encouraged to quit and approximately 20 million try to quit each year, it is essential to learn how quitting and continued smoking are related to mental health status, disease status and progression, quality of life, and late relapse. It is equally important to be able to identify risk factors for these important outcomes so we can better assist smokers to successfully quit, prevent relapse, and improve mental and physical health.

1. **Preliminary Studies**

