| Fagerström Test of Nicotine Dependence (FTND) | X |  |  |  |  |  |
| Wisconsin Smoking Withdrawal Scale (WSWS) | X | X | X | X | X | X |
| Multidimensional Personality Questionnaire-Short Form (MPQ-S) | X |  |  |  |  |  |
| Positive and Negative Affect Scale (PANAS) | X | X | X | X | X | X |
| Depression Proneness Inventory (DPI) | X |  |  |  |  |  |
| Holmes-Rahe Social Readjustment Rating Scale | X | X |  | X |  | X |
| International Physical Activity Questionnaire (IPAQ) | X | X |  |  |  | X |
| PrimeScreen (dietary questionnaire) | X | X | X | X | X | X |
| Food Frequency Questionnaire (FFQ) | X | X |  | X |  | X |
| Vital Signsa | X | X | X | X | X | X |
| Suicidality Assessment | X | X |  | X |  | X |
| Complete Physical Exam | X |  |  |  |  |  |
| Waist Circumference | X | X |  | X |  | X |
| National Comorbidity Survey – Revised (NCS-R-CIDI)b | X | X |  | X |  | X |
| Short Inventory of Problems (SIP-2R) – Alcohol related problems | X | X | X | X | X | X |
| Social Network Interview | X | X |  | X |  | X |
| Kansas Marital Satisfaction Scale c | X | X |  | X |  |  |
| Quality of Life Inventory (QOLI) | X | X |  | X |  | X |
| Pregnancy Test for women | X |  |  |  |  |  |
| Ultrasound Carotid Intima–Media Thickness (CIMT) | X |  |  |  |  | X |
| Ultrasound Brachial Artery Response Test (UBART) | X |  |  |  |  |  |
| Exercise Stress Test | X |  |  |  |  | X |
| Pedometer Training and Assessment | X | X |  | X |  | X |
| Blood Drawd | X | X |  |  |  | X |
| Smoking Statuse | X | X | X | X | X | X |
| **Time Required For Each Visit (in hours)** | **8** | **4** |  | **2** |  | **4** |

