*Data Acquisition and Preparation.*Data will be inspected on a continuous basis over the course of the study to ensure that data acquisition is satisfactory. Virtually all of the data will be captured via computer entry, scannable forms and palm-top computers. One further data source will be data obtained from medical tests. These typically do not generate computer data files and when they do not, they will be double-entered.

*Data Comparisons.*This study will permit us to address numerous important questions about how quitting smoking and relapse are related to health and psychosocial outcomes, and for whom particular outcomes are especially likely. We cannot outline all of the analyses permitted by this data set. However, we will present analytic plans for several important outcomes. These will reveal the strategies that we will use and the relations to be tested.

We will identify a critical question, use regression methods to identify significant predictors of ultimate endpoints, and then use structural models to explore more complex relations among significant predictors across time. We will assess genetic correlates of critical phenotypes (e.g., nicotine dependence, quitting success, mental health status, and atherosclerosis status and progression) in a parallel research track. We will eventually combine genetic and nongenetic variables in integrated prediction models to determine potential mediators of genetic relations (e.g., via personality) and whether candidate genes predict particular endophenotypes (e.g., smokers reporting escalating or prolonged withdrawal124,125). Construction of genetic models will follow the principles outlined below.

*Predicting Discrete Endpoints.*Many clinicians and others interested in public health will primarily be interested in best-fitting models that predict outcomes (e.g., psychiatric diagnostic outcomes such as depression, or diagnoses such as diabetes, quality of life) at some future point in time. To address the prediction of outcomes at discrete points in time, we will use logistic and multiple regression models (for categorical & continuous dependent variables, respectively) in which ultimate status at Year 2 or 3 is predicted by both prequit and postquit variables.

In testing predictive relations we will follow a general strategy consistent with the model building recommendations made by Hosmer & Lemeshow.277

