- We will identify on an a priori, substantive basis, the major predictors to be tested, control variables, and critical interactions. Predictors will include both static and dynamic variables gathered both before and after the quit attempt.
- We will then examine distributions and use transformations where appropriate.
- Missingness will be addressed through direct Maximum Likelihood estimation278 assuming that ignorability assumptions are appropriate and standard error and test statistics are robust.279
- We will test univariate relations for all substantive variables so that their nonresidualized relations may be reported. Univariate variables will be modeled in various ways discussed in the section “Representing Constructs”) in order to determine the generalizability of obtained relations.
- We will use model-building procedures described below to identify best-fitting models using all promising candidate measures identified in univariate analyses.
- We will engage in *secondary analyses* to explore the relations of other variables with important targeted outcomes. These analyses will explore models that are less clinically or theoretically important than those tested in primary analyses, but ones that may provide the basis for future hypotheses and research. If reported, secondary analyses will clearly be labeled as exploratory.

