Hypothesis 3. Smoking cessation/reduction will lead to improved *quality of life*. We expect continuing smokers to report diminishing QOL levels over the follow-up period (relative to baseline), and we expect exsmokers to report improving QOL. Change will be measured from baseline levels of tested measures (e.g., Quality of Life Questionnaire or other QOL indicator: e.g., 30 day functioning). *Individual differences and control variables*: Improvement in QOL will be inversely related to age.  *Modifiable risk factors:* QOL improvements will be inversely related to postquit heavy drinking days, postquit increase in BMI, post-quit measures of physical health symptoms (CIDI Chronic Conditions & 30 Day Symptoms) and positively related to postquit social support available in the social network. We make a further prediction that much of the improvement in QOL will be mediated by postquit psychiatric symptoms/disorders. We predict that the influence of smoking on QOL will be moderated by postquit weight gain/BMI as those gaining more weight will show a reduced relation between cessation and QOL improvements.11

Hypothesis 4.Smoking relapse late in the follow-up period (>1 yr postquit) will be related to presence of alcohol use in the person’s social network/dyad and to presence of smokers in the social network/dyad and alcohol use. Late relapse will be modeled both as 3-year point-prevalence or latency from 1-year post-quit. *Individual differences and control variables*: Importantly, baseline nicotine dependence will *not* predict late relapse, nor will female gender (although this may be because these factors may have already exerted their influence in the first year of follow-up which we will examine). *Modifiable risk factors:* We expect late relapse likelihood will be positively related to both number of drinking days and heavy drinking days (both postquit), to number of smokers in the social network and contact with such smokers (postquit), and to spousal smoking among partnered participants.

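### Hypothesis 4 does not require network and spousal predictors of late relapse to be measured before the relapse, so consequences of relapse may be reported as precipitants

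*Protocol*

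**What the plan says.** Hypothesis 4 (Protocol, Analytic Plan, Principal Hypotheses) gives the outcome in two forms: "Late relapse will be modeled both as 3-year point-prevalence or latency from 1-year post-quit". It expects late relapse to be positively related "to number of smokers in the social network and contact with such smokers (postquit), and to spousal smoking among partnered participants". The participant's own drinking is dated in the same way: "positively related to both number of drinking days and heavy drinking days (both postquit". Alcohol use in the network is named in the hypothesis's opening sentence with no time window, and spousal smoking also has none. Baseline nicotine dependence and female gender are predicted not to matter.

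The general rules do not narrow this. Under Predicting Discrete Endpoints, "ultimate status at Year 2 or 3 is predicted by both prequit and postquit variables". The model-building list adds: "Predictors will include both static and dynamic variables gathered both before and after the quit attempt". Both date a predictor by the quit attempt, not by the relapse.

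In Table 4 the row "Social Network Interview" is marked at orientation and at the one-, two- and three-year visits, and not at the 18- and 30-month calls.

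The significance section states the intended use: "This research will also elucidate the precipitants of late relapse".

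**The concern.** Every network interview from month 12 onward counts as postquit, but for someone who relapses late some of them describe life after the relapse. If relapse brings a person back among smokers, those interviews create the predicted association even when nothing about the network came before the relapse.

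The protocol itself entertains network change in response to smoking status. Its background section asks: "Does quitting, in fact, cause smokers to lose smoking friends". Its secondary analyses list smoking and alcohol use in the network as postquit outcomes.

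The bias would run one way. Hypothesis 4 contrasts social factors, which relapse may alter, with baseline dependence and gender, which it cannot. Any reverse effect therefore supports the claim that late relapse is social in origin. The protocol's tentative suggestion that relapse prevention might concentrate on the person's environment would rest on that contrast.

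**Working it through.** **1. Time order.** The interviews set against the time of relapse:

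| Relapse occurs | Month 12 | Month 24 | Month 36 |
|---|---|---|---|
| Year 2 (months 12-24) | before | after | after |
| Year 3 (months 24-36) | before | before | after |

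Only month 12 comes before relapse in both rows. Both outcome codings are compatible with month-12 predictors, but neither requires them.

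**2. Number of late relapsers.** Inputs from the protocol: about 360 abstainers entering Project 2, 4% relapse a year (range given 3-5%) and 5% attrition a year.

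- Check against the plan's own figures: 360 × 0.91² = 298 (or 360 × 0.95² × 0.96² = 299), against 300 stated; 540 × 0.91² = 447, against 450; 900 × 0.95² = 812, as stated. The inputs reproduce the plan.
- Year 2: 360 × 0.04 = 14.4. Year 3: 360 × 0.91 × 0.04 = 13.1. Total 27.5.
- Among retained abstainers: 360 × 0.95² = 325, of whom 325 × (1 − 0.96²) = 25.5 relapse.

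**3. Illustration of size.** Assume no effect of the network on relapse, and that relapse shifts later network scores by d SD. The documents give no value for d, so a range is shown.

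Closed form, 28 relapsers against 300 abstainers: SE = √(1/28 + 1/300) = 0.198.

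- Month-36 value: the shift is d. At d = 0.5, 0.5/0.198 = 2.53 and the chance of |z| > 1.96 is 0.72.
- Mean of months 12, 24 and 36: two of three interviews follow a year-2 relapse and one of three a year-3 relapse, so the average share is (14.4 × 2/3 + 13.1 × 1/3)/27.5 = 0.51, about half. At d = 0.5 the shift is 0.25, 0.25/0.198 = 1.26, and the chance is 0.24.

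Simulation: 3,000 runs, 325 abstainers, 4% relapse a year, assumed correlation 0.7 between adjacent visits, two-sided t test at 0.05.

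| Predictor | d = 0 | d = 0.25 | d = 0.5 | d = 0.8 |
|---|---|---|---|---|
| Month 12 | 0.06 | 0.06 | 0.05 | 0.04 |
| Mean of months 12-36 | 0.05 | 0.11 | 0.29 | 0.61 |
| Month 36 | 0.04 | 0.22 | 0.67 | 0.96 |

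For the three-visit mean the two methods differ (0.24 and 0.29) because the closed form gives the mean an SD of 1. At correlation 0.7 its variance is (3 + 2 × (0.7 + 0.7 + 0.49))/9 = 0.753, so its SD is 0.87 and the standardised shift is larger. Over 3-5% relapse a year, the month-36 rate at d = 0.5 runs from 0.56 to 0.75.

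**4. Existing safeguards.** Under Hypothesis 5 the protocol concedes that the regressions do not show the order of drinking and smoking, and it sends that question to structural models. Those include an autoregressive trajectory model in which drinking predicts later smoking and the reverse. No such step is named for network or spousal smoking. The worked example (Figure 5 text) enters postquit network smoking as an exogenous predictor of the smoking trajectory.

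**The case against.** The strongest reply is that postquit only separates these measures from prequit ones and does not select a visit. The month-12 interview is postquit, and latency from year 1 starts at that visit. Choosing the wave or lag could be left to a statistical analysis plan. This stands far enough that the outcome is a risk and not a certainty. A reader might infer that consequences of relapse will be reported as causes; the text does not support that, because it nowhere says that post-relapse interviews will be used. The point remains because the protocol does state a window, and that window admits values taken after the relapse.

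Second, a reader might infer that the protocol ignores temporal order. It does not. For every critical question it plans regression first and then structural models of significant predictors over time, with reciprocal relations in view. Four in-person measurements make the network interview eligible. The participant's own drinking is therefore largely answered. For the network, no reciprocal model is named and the only example treats it as exogenous.

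Third, Aim 4 speaks of factors associated with late relapse, the Limitations section disclaims causal certainty, and each contact records the context of any relapse. These soften the point. However, the context items have no comparison group among those who stayed abstinent, and the significance section still promises precipitants.

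Fourth, the illustration uses shifts and predictor codings that the protocol does not specify. That is correct, and limits what the percentages can be used for.

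**Conclusion.** The point holds in a limited form. As written, Hypothesis 4 admits network smoking, contact with smokers, network alcohol use and spousal smoking measured after the relapse they are meant to explain. Any such reverse effect would favour the hypothesis. The gap is clearest for network and spousal smoking and much smaller for the participant's own drinking.

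At an assumed 0.5 SD shift, about 27 late relapsers and no true effect, a nominal 5% test would reject in about 24-29% of studies with the three-visit mean and 67-72% with month 36. With month 12 it stays near 5%. These are not the study's expected error rates: they depend on the assumed shift and on which visit is used, and at zero shift the inflation vanishes. That relapse raises network smoking is an extension of the protocol's question about quitting, and it is least obvious for a spouse's smoking.

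**What to change.** Add to Hypothesis 4:

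- **Latency model:** enter each time-varying predictor as a lagged covariate from the last contact before the relapse date on the time-line follow-back record. For network items this is month 12 for relapse between months 12 and 24, and month 24 for later relapse. Months 18 and 30 can be used for items asked by telephone, such as recent alcohol use.
- **3-year point prevalence:** use month-12 predictors only.
- **Associations at the same contact or later:** report them as descriptive and non-directional.

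This needs only analysis wording, since the visits and smoking dates are already planned. The cost is older predictor values: up to 12 months old for network items in the latency model (relapse late in an interval), and 24 months old at the 3-year endpoint. A true effect of recent network change could be diluted.

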## In the current study, we will use a more sensitive measure of carotid IMT (CIMTmax ) that averages segmental maximum carotid wall thicknesses from all measurable carotid artery segments (up to a maximum of six segments). Bots et al.288 recommended CIMTmax for intervention trials and also computed pooled estimates of the annual rate of CIMT change across multiple atherosclerosis trials. These pooled estimates were then used to compute sample size estimates for intervention trials. We use these same pooled estimates of CIMTmax change in power calculations for the current study. Other assumptions include: =.05, a 20% difference in CIMT progression between abstinent participants (N = 300) and continuing smokers (N = 450), and use of the CIMTmax measure with an estimated change in CIMT for continuing smokers of 5.28 m (SD= 5.0 m).288 Based on these assumptions, we will have power of .81 to detect a 20% difference in progression between abstinent and smoking participants. This is a conservative power estimate as control variables should reduce error and our N is likely to exceed 750, and the projected effect size is smaller than that reported by Howard et al.1 Thus, we believe that the current study is adequately powered to detect predicted differences in CIMT progression over three years for the comparison of smokers versus continuously abstinent ex-smokers. Analyses of continuous measures of post-quit smoking also may yield greater power.

